***Allowance for data dependent stopping:***

We propose using formal interim analysis methods for monitoring the primary outcome (incidence of HIV infection) as well as the safety aspect of the study. Lan‑DeMets group sequential methods with O'Brien‑Fleming bounds 117,118 will be utilized to ensure the maintenance of an overall Type I error rate of 5%. For monitoring HIV incidence, we anticipate one interim analysis to allow DSMB to decide whether we can commence circumcisions in the control arm, and allow sufficient time for completion of control surgeries before the end of the project. Assuming an interim analysis at project month 40, we will accrue a total of 3,028 py observation per arm, which represents 77% (3028 * 2 / 3932 * 2) of the information to be accumulated during the trial. This information fraction, for example, will give sequential O'Brien‑Fleming boundaries equal to 2.303 for the interim analysis and 2.017 for the final analysis. Without using these boundaries, we estimate (via simulation with 10,000 runs) that the overall Type I error rate wouldl be inflated to approximately 7.7%. Using these boundaries, we estimate that the Type I error rate is maintained at 0.05 and that the power for a RR of 0.53 is equal to 89.5%. Furthermore, with this RR, we estimate that there is approximately a 70% chance of crossing the boundary at the interim analysis. Sequential confidence intervals 118a will be used when reporting results. The investigators will be blinded for the interim analysis. Monitoring of safety will be done similarly, except that it will occur on a continuous basis, and will use the methods of Lan *et al.*

***Age criteria and selection of high risk groups:***

Rakai has is a mature generalized epidemic setting with relatively high incidence throughout the population. Table 5 shows male age-specific HIV incidence. Incidence is lowest among adolescents, high and sustained among men aged 20-29, and declines modestly at older ages. Exclusion of adolescent men 15-19, would exclude a group with considerable HIV incidence and which is of great importance in future programs. Restricting enrollment to the highest risk age group (20-29 years) would marginally increase incidence relative to the total male population 15-49, but would only include 39.5% of all men. Enrollment restricted to men aged 20-29 would require adding many more communities in order to maintain power, but this complicates logistics and inflates costs. Moreover, acceptability was highest (65% in ages 20-29), so self-selective acceptability would automatically over sample these highest risk age groups. We therefore proposed to enroll all consenting men aged 15-49.

***Additional Power provided by the ~ 1,000 HIV-negative men who decline VCT, enrolled in the Gates sponsored trial and approximately 500 additional HIV-negative men enrolled into the Gates trial after NIH trial enrolment is completed.***

Prior analyses have shown that persons who refuse VCT have higher risk behaviors than persons who accept VCT, and that this difference in risk profile is reflected in higher HIV incidence among the former populations. (HIV incidence was 1.5/100 py in men declining VCT versus 1.3/100 py in men accepting VCT.

We estimated that about 400 HIV-negative men would decline VCT per arm, assuming the loss to follow up and cross over rates above, we anticipated that these men would add an additional ~ 1256 py per arm, to the person time contributed by the HIV- men enrolled in the NIH trial. Thus, the total person years observation contributed by the combined populations of HIV-negative men from the two trials is 5188 py (1256 + 3,932 py per arm). This would enhance the study power to detect a lesser efficacy of circumcision, and help guard against loss of power if the assumptions regarding follow up and cross-over prove to be too conservative.

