## Male STDs and STD Symptoms:

These estimates are based on the total populations of HIV- negative men enrolled in the Gates and NIH trials.

*STDs:*

All participants will be tested for HIV and syphilis at all study rounds. For budgetary reasons, additional specimens will be collected for selective STD testing with other funds. (Please see laboratory methods). From prior data the expected infection rates are: syphilis prevalence ~10% and incidence 2.2/100 py. The RR for syphilis in circumcised versus uncircumcised men was 0.71. With 5492 observations per arm, we have >80% power to detect a RR of 0.70 for the effects of circumcision on syphilis prevalence, and >80% to detect a RR = 0.5 in syphilis incidence.

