***STD symptoms:***

The RR for GUD in HIV-negative circumcised versus uncircumcised men was 0.70. With 2,500 men enrolled per arm in the NIH funded study, and approximately 1,100 per arm in the Gates-funded study, and 85% follow up, we have 85% power to detect a difference of this magnitude. The RR of balanitis in all circumcised versus uncircumcised men was 0.53 (prevalence 11.6% in circumcised and 22.8% in uncircumcised), and we have 98% power to detect an effect of this magnitude. Therefore, these sample sizes are adequate, even with cross-over effects.

Thus, the study is adequately powered to detect reductions in STDs and STD symptoms in the circumcision relative to the control arm.

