## Proposed involvement of Human Subjects:

The trial participants will be 1000 uncircumcised adolescent and adult men who decline VCT (of whom ~ 200 will be HIV+ positive and 800 HIV- negative), and ~ 800 HIV-positive men, aged 15-49, resident in Rakai communities in southwestern Uganda. We have excluded uncircumcised boys under age 15, because the low HIV incidence in such youngmales would not add to the study power, and we wish to establish safety and efficacy at older ages, before assessing circumcision in boys under age 15. The RCCS participants will be ~6000 women and ~ 3000 men enrolled in the cohort.

In the trial, men consented for screening and if found to be eligible, they consented for enrollment. Consenting men were randomly assigned to an immediate circumcision arm (intervention arm) in which they were offered the service within approximately 1 month of enrolment, and to a delayed circumcision (control arm), in which they were offered circumcision approximately 24 months after enrolment. Circumcision is carried out by trained and supervised physicians. Participants are monitored after surgery to maximize care. Men in both arms are interviewed and asked to provide biological samples at enrolment and at 6,12 and 24 month visits

Interview information is obtained at baseline, time of surgery and at each follow up visit and includes sociodemographic characteristics, risk behaviors (e.g., number and type of partners, condom use, sexual networks, alcohol use, coercive sex), health information including symptoms of STDs or penile pathology (e.g., discharge, dysuria, GUD, balanitis, post-operative infection or bleeding), and symptoms suggestive of OIs or AIDS (e.g., weight loss, chronic diarrhea, cough, KS etc). Most questions have already been tested in prior Rakai Health sciences Program surveys.

Blood samples are collected from men for detection of HIV, STDs and hemoglobin as per protocol . Male urine sample is collected for detection of STDs with other funds. Prior to surgery, subpreputial swabs are obtained for assessment of STDs as per protocol and men reporting GUD are asked for an ulcer swab for M-PCR with other funds. The foreskin of circumcised men are retained for histopathology.

Subjects are identified by a permanent study ID number on all forms and samples, and a polaroid photograph is used to insure identity during follow up.

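### Gates HIV-negative person-time is entered per arm at its two-arm value (1,256 instead of 629 py), and Section 8.3 uses Gates counts larger than the HIV-negative population it names

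*Protocol*

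**What the plan says.** Section 8.2, in the paragraph on additional power from the Gates trial, takes "about 400 HIV-negative men would decline VCT per arm" and says "we anticipated that these men would add an additional ~ 1256 py per arm". It then gives the combined person-time of the HIV-negative men in the two trials: it "is 5188 py (1256 + 3,932 py per arm"). The paragraph's heading also names approximately 500 further HIV-negative men who enter the Gates trial once NIH enrolment is complete. Section 10.4 splits the 1,000 men who decline VCT: "of whom ~ 200 will be HIV+ positive and 800 HIV- negative". That is 400 HIV-negative men per arm.

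Section 8.3 opens with "These estimates are based on the total populations of HIV- negative men enrolled in the Gates and NIH trials". For syphilis it states: "With 5492 observations per arm, we have >80% power to detect a RR of 0.70 for the effects of circumcision on syphilis prevalence". For GUD it takes 2,500 NIH men per arm plus "approximately 1,100 per arm in the Gates-funded study, and 85% follow up, we have 85% power to detect a difference of this magnitude", the magnitude being a ratio of 0.70. It gives no control-arm GUD prevalence.

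**The concern.** Two years of follow-up cap the contribution of 400 men at 800 py even if nobody is lost, so 1,256 py per arm cannot come from the men the sentence names. If a two-arm figure has been added to a one-arm figure, the combined total is too high. Section 8.3 then gives the same HIV-negative Gates population two further sizes, both larger.

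Section 8.2 offers the combined total as the reason the Gates men add power and protect against shortfalls, and Section 8.8.1 plans an analysis of the combined HIV-negative population. Section 8.3 concludes from its bases that the study is adequately powered for STDs and STD symptoms. Anyone who later cites these passages when interpreting a null result in HIV-negative men would rely on denominators that do not agree with each other.

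**Working it through.** **Person-time rule.** Section 8.2 assumes two years of follow-up and 15% annual loss. Its NIH figure shows how person-years are counted: n × 0.85 in year 1 plus n × 0.85² in year 2, i.e. n × 1.5725.

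- NIH, 2,500 per arm: 2,500 × 1.5725 = 3,931 (stated 3,932).
- Discordant couples in Section 8.4, 220 per arm: 220 × 1.5725 = 346 (stated 344).

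The rule therefore reproduces two of the protocol's own figures.

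**Gates HIV-negative men.** The same rule, with the total after adding 3,932:

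| Gates men per arm | Basis | Gates py per arm | Combined py per arm | Excess of 5,188 |
|---|---|---|---|---|
| 400 | Number in the sentence; Section 10.4 | 629 | 4,561 | 13.7% |
| 650 | 400 plus half of ~500 | 1,022 | 4,954 | 4.7% |
| 750 | Half of ~1,000 plus half of ~500 | 1,179 | 5,111 | 1.5% |

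Entering 800 men, the two-arm total, gives 1,258, which matches the stated 1,256.

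**Bases in Section 8.3.** The summary table of the two trials lists ~1,000 HIV-negative decliners and ~500 HIV-negative acceptors in the Gates trial, so at most 1,500/2 = 750 per arm.

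- 5,492/1.5725 = 3,493 men per arm. Less 2,500 NIH men this leaves about 993 Gates men per arm. Section 3.1.1 reports ~997 HIV-positive and ~1,000 HIV-negative Gates men, about 1,000 per arm with both groups counted.
- About 1,100 per arm is close to half of all Gates men in the summary table: (800 + 1,000 + 500)/2 = 1,150.

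Both bases fit a Gates population that includes HIV-positive men.

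**Effect on power (two-sided 0.05).**

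*HIV.* For two Poisson rates, power = Φ[(r₁ − r₂)/√((r₁ + r₂)/py) − 1.96], with r₁ = 1.8/100 py from Section 8.2. The rate ratio detectable with 80% power is 0.58 at 3,932 py, 0.61 at 4,561 and 0.63 at 5,188.

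*Prevalence outcomes.* Power = Φ[(|p₁ − p₂| − 1.96·SE₀)/SE₁], with SE₀ pooled and SE₁ unpooled. The corrected base is (2,500 + 400) × 0.85 = 2,465 followed per arm, or (2,500 + 750) × 0.85 = 2,762.

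- Syphilis prevalence, 10% against 7%: 96.6% at 2,465 (stated >80%).
- Syphilis incidence, 2.2 against 1.1/100 py, by the rate formula: 98% at 4,561 py (stated >80%).
- Balanitis, 22.8% against 11.6%: about 100% at 2,465 (stated 98%, which needs only 362 per arm).
- GUD, ratio 0.70: the stated 85% at 3,600 × 0.85 = 3,060 per arm implies a control prevalence of about 5.3%. At that prevalence power is 77% at 2,465 and 81% at 2,762.

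The 5.3% is back-solved, so the GUD result is also shown over an assumed range:

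| Control GUD prevalence (assumed) | 3,060 per arm | 2,762 per arm | 2,465 per arm |
|---|---|---|---|
| 4% | 74% | 69% | 64% |
| 5% | 83% | 79% | 74% |
| 6% | 89% | 86% | 82% |
| 8% | 96% | 94% | 92% |

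**The case against.** The strongest defence is that little depends on these figures. No numerical power is attached to 5,188 py. The 89.5% power and the monitoring boundaries in Section 8.2 rest on the NIH 3,932 py alone, and Section 8.1 says that the NIH trial is independently powered and that the Gates men cannot support an HIV endpoint by themselves. Enrolment closed in December 2006, and the NIH trial had already stopped for efficacy. All of this stands, and it limits the seriousness of the point.

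A second defence is that the heading covers more than the 400 men per arm. That is fair, and it makes 13.7% the upper end of a range. It does not rescue the figure: the sentence credits the person-time to the 400 per arm, and even 750 per arm fall short under the protocol's rule. Crediting half a year to men who are lost would bring 750 men to about 1,283 py, but the same rule would turn the NIH 3,932 into 2,500 × 1.71125 = 4,278.

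A third defence is that Section 8.1 lists STD acquisition in both HIV-negative and HIV-positive men as an endpoint, so in Section 8.3 the population label may be wrong rather than the counts. This is plausible, and the fix must allow for it.

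A reader might go further and infer that the STD power claims in general are overstated, or that the syphilis claim fails. The documents do not support this. Both syphilis statements and the balanitis statement survive the smaller base. Section 8.3 quotes a syphilis ratio of 0.71 without calling it an incidence ratio, so low power for incidence at 0.71 would not contradict a stated claim. Nor can one say that a prevalence ratio of 0.70 is unattainable because seropositivity persists. With 10% at baseline, 2.2/100 py and complete protection, the two-year ratio is about 0.72, but with 9% it is 0.697, and the protocol gives the prevalence only as approximately 10%.

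**Conclusion.** The error in Section 8.2 is established from the protocol's own inputs. The per-arm contribution of the 400 men named is 629 py, 1,256 is the two-arm total, and the combined per-arm figure is 4,561, not 5,188. On the widest reading of who is counted the total is 5,111, so 5,188 is too high by between 1.5% and 13.7%.

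The bases in Section 8.3 contradict the section's own HIV-negative label, since the Gates trial has at most about 750 such men per arm. That they include HIV-positive men is the likeliest reading, not a proven one.

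The effect on power is slight for HIV (detectable ratio about 0.61 instead of 0.63) and leaves the syphilis and balanitis statements intact. The 85% for GUD would be about 77% to 81% if the control prevalence is the implied 5.3%; without a stated prevalence no single corrected value can be given. This is a minor correction.

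**What to change.** - **Section 8.2:** replace 1,256 by 629 and 5,188 by 4,561 py per arm, or show the person-years for the HIV-negative men actually enrolled, with the number per arm used.
- **Section 8.3, population:** either replace 5,492 and about 1,100 by counts derived from HIV-negative men per arm, or relabel the population as including HIV-positive men. State how 5,492 is obtained.
- **Section 8.3, GUD:** restate the 85% on the corrected base together with the control prevalence assumed. If the implied 5.3% is used, this is about 77% with 400 and 81% with 750 Gates men per arm.
- **No change on this ground** to the syphilis and balanitis power statements.

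The cost is a few figures and sentences in two sections. Design, sample size, monitoring boundaries and analysis methods are unaffected.

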## Male STDs and STD Symptoms:

These estimates are based on the total populations of HIV- negative men enrolled in the Gates and NIH trials.

*STDs:*

All participants will be tested for HIV and syphilis at all study rounds. For budgetary reasons, additional specimens will be collected for selective STD testing with other funds. (Please see laboratory methods). From prior data the expected infection rates are: syphilis prevalence ~10% and incidence 2.2/100 py. The RR for syphilis in circumcised versus uncircumcised men was 0.71. With 5492 observations per arm, we have >80% power to detect a RR of 0.70 for the effects of circumcision on syphilis prevalence, and >80% to detect a RR = 0.5 in syphilis incidence.

***STD symptoms:***

The RR for GUD in HIV-negative circumcised versus uncircumcised men was 0.70. With 2,500 men enrolled per arm in the NIH funded study, and approximately 1,100 per arm in the Gates-funded study, and 85% follow up, we have 85% power to detect a difference of this magnitude. The RR of balanitis in all circumcised versus uncircumcised men was 0.53 (prevalence 11.6% in circumcised and 22.8% in uncircumcised), and we have 98% power to detect an effect of this magnitude. Therefore, these sample sizes are adequate, even with cross-over effects.

Thus, the study is adequately powered to detect reductions in STDs and STD symptoms in the circumcision relative to the control arm.

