***Efficacy:***

The Rakai STD Control Study78 found an incidence of 1.8/100 PY among the uncircumcised men and 0.9/100 PY among the circumcised men, with a Poisson adjusted RR = 0.53.1 We base our sample size estimates on this efficacy, and use a two-sided test with  = 0.05 and 1- = 0.80.

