***Assumptions:***

We assumed two years follow up, with participants enrolled between 9-26 months of the study and follow up completed by study month 50, and an annual loss to follow up of 15% (please see feasibility). We also estimated the loss of power due to possible contamination (i.e., cross-over) of 7.5-10%.

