## Analysis Plan

### Primary Endpoint, HIV incidence in Males.

This analysis will be done separately for HIV-negative men enrolled in the Gates and NIH trials, and for the combined population of HIV-negative males enrolled in both trials.

HIV incidence per 100 person-years (PY) will be estimated, assuming seroconversion occurred at the mid-point of each follow up interval. In both arms, time from enrollment will be accumulated up to 24 months of follow up. Person time will discount the postoperative period of sexual abstinence for intervention arm subjects. Baseline samples of subjects who seroconvert during the first follow up interval will be tested by detuned EIA and PCR to detect prevalent infections during the window period, and any suspected prevalent cases will be excluded from incidence analyses.

Exploratory data analysis will examine the populations in the two arms at enrollment to assess baseline comparability. HIV incidence will be determined by strata of covariates such as age, marital status, behaviors (e.g., number of partners, condom use), health status and other variables to identify potential confounders. We will also assess contamination (i.e., cross-over) among men allocated to circumcision who do not receive surgery, and among control subjects who opt to have circumcisions performed from non-Project services.

An intent-to-treat approach will be taken, and all men who enroll will be included, irrespective of whether intervention arm participants ultimately receive circumcision, or whether control arm participants crossover and receive circumcision prior to 24 months follow up. The rationale is that a proportion of enrolled men who initially accept circumcision may change their mind prior to receipt of surgery, and such men are likely to be self-selected. Because circumcision is delayed in the control arm, such self-selection could be differential between randomization groups. Therefore, in the circumcision arm, enrolled men who subsequently refuse circumcision, will be ascribed half the person time from enrollment to scheduled date of circumcision.

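### The protocol's statement that the sample is adequate despite cross-over is not supported for genital ulcer disease (GUD): the stated 85% power makes no allowance for cross-over and falls to about 78–81% or 67–72%, depending on which arms cross over

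*Protocol*

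**What the plan says.** Section 8.3 of the protocol, under STD symptoms, takes its GUD effect from a comparison by circumcision status: "The RR for GUD in HIV-negative circumcised versus uncircumcised men was 0.70". The sample is described as "With 2,500 men enrolled per arm in the NIH funded study, and approximately 1,100 per arm in the Gates-funded study, and 85% follow up", and the power claim follows directly: "we have 85% power to detect a difference of this magnitude". The paragraph then gives 98% power for balanitis (prevalence 11.6% in circumcised and 22.8% in uncircumcised men) and closes with "Therefore, these sample sizes are adequate, even with cross-over effects". A final sentence says the study is adequately powered for STDs and STD symptoms in the circumcision arm relative to the control arm.

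Section 8.2 supplies the cross-over range under Assumptions: "We also estimated the loss of power due to possible contamination (i.e., cross-over) of 7.5-10"%. The paragraph on contamination in the same section writes two dilution formulas as if they were equal, and works one example, 0.53 becoming 0.55 at 7.5%. Section 8.4 works a second, 0.39 becoming 0.41.

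The analysis plan for male HIV incidence (8.8.1) is by intention to treat and includes all enrolled men "irrespective of whether intervention arm participants ultimately receive circumcision, or whether control arm participants crossover and receive circumcision prior to 24 months follow up". Section 6.1a also classifies a man randomised to circumcision who has decided against surgery by 6 months as a cross-over.

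**The concern.** The effect of 0.70 is by status, but the trial compares randomised arms. Cross-over pulls the arms together, so the between-arm effect is weaker than 0.70 and the power is below 85%. The protocol shows this step for female HIV acquisition in section 8.4, where 85% power at the undiluted ratio becomes 80% after 7.5% contamination. It does not show it for GUD, yet draws the same conclusion of adequacy. The sentence follows the balanitis result, where the effect is large enough to survive dilution, and extends that comfort to an endpoint with much less margin.

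GUD is one of the secondary endpoints in section 8.8.3. A null GUD result would be read more firmly than it deserves if readers believed the 85% already survived cross-over.

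**Working it through.** **Inputs.** Section 8.3: RR 0.70; 2,500 + 1,100 = 3,600 men per arm; 85% follow-up, so 3,600 × 0.85 = 3,060 per arm; power 85%. Section 8.2: cross-over p = 7.5–10%; two-sided test with alpha 0.05 and 80% power (stated for male HIV incidence, assumed here for GUD). Intention to treat is likewise stated for HIV incidence and assumed for GUD.

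**Can the 85% be reproduced?** No, because no GUD rate is given. With 3,060 per arm and RR 0.70, a two-proportion test has power 61% at a control rate of 3%, 83% at 5%, 89% at 6% and 96% at 8%. The control rate that returns 85% is 5.29%, with 0.70 × 5.29% = 3.70% in circumcised men, a difference of 1.59 points. I use this as the anchor.

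**Dilution formulas.** Section 8.2 equates these two:

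- Both arms: RR* = (p + (1−p)·RR) / (p·RR + (1−p))
- Controls only: RR* = RR / (p·RR + (1−p))

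They are not equal. The protocol's worked values show which was used, at p = 7.5%:

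| True RR | Both arms | Controls only | Protocol |
|---|---|---|---|
| 0.53 | 0.586 | 0.549 | 0.55 |
| 0.39 | 0.457 | 0.409 | 0.41 |

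The worked values follow the controls-only form.

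**Quick check for equal cross-over in each arm.** Power of 85% at two-sided 0.05 means an expected z of 1.960 + 1.036 = 2.996. The between-arm difference shrinks by (1 − 2p), while the variance hardly changes.

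- p = 7.5%: 2.996 × 0.85 = 2.547; 2.547 − 1.960 = 0.587; power 72%.
- p = 10%: 2.996 × 0.80 = 2.397; 2.397 − 1.960 = 0.437; power 67%.

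**Full calculation** (n = 3,060 per arm, anchored at 85%). For example, with 7.5% in each arm the control rate is 5.29 − 0.075 × 1.59 = 5.17%, the intervention rate is 3.70 + 0.075 × 1.59 = 3.82%, and RR* is 0.739.

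| Who crosses over | RR* at 7.5% | Power | RR* at 10% | Power |
|---|---|---|---|---|
| Controls only | 0.716 | 79.6–80.6% | 0.722 | 77.6–78.9% |
| Intervention arm only | 0.723 | 78.6% | 0.730 | 76.2% |
| Total p split equally between arms | – | 79.1% | – | 76.9% |
| Same p in each arm | 0.739 | 72.1% | 0.753 | 66.9% |

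The controls-only range reflects whether the control rate is itself diluted (lower figure) or RR* is applied to the undiluted control rate (higher figure).

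**Sensitivity.** Once power is anchored at 85%, the results move by about 0.001 for 2,125 to 5,492 men per arm. A Poisson version gives 72.3% and 67.1% for equal cross-over in each arm. A one-sided test would give 73.7% and 69.1%.

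**Balanitis.** With 10% cross-over in each arm, the rates become 22.8 − 0.10 × 11.2 = 21.7% and 11.6 + 0.10 × 11.2 = 12.7%. Power stays near 100%, so the adequacy statement holds there.

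**The case against.** The strongest reply is that 72% and 67% are not simply the protocol's own figures. They require 7.5% or 10% cross-over in each arm, and no section sets a per-arm rate. Both worked dilutions use the controls-only form. On that form GUD power is about 80% at 7.5% and one to two points short at 10%, against an 80% convention, which is borderline rather than a failure. This stands, and it limits the conclusion.

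A second reply is that everything rests on an 85% that cannot be checked. The neighbouring balanitis figure gives reason for care: its stated prevalences with 3,060 men per arm imply power near 100%, not 98%, so the method behind these figures is unclear. The 85% might contain an allowance that is not mentioned. This also stands as a caveat. However, the text ties the 85% to the undiluted 0.70 and names only follow-up, and section 8.4 uses the same pattern with cross-over applied as a separate step.

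A third reply is that enrolment has closed and no design decision changes. That is true. What remains is how a GUD result will be read.

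A reader might infer that GUD is the main STD-symptom endpoint, or that the planned work on mediation of the HIV effect inherits this power loss. The protocol supports neither. GUD is listed with discharge/dysuria among secondary endpoints, and the mediation work starts from associations of STDs and symptoms with incident HIV, whose power is not the arm-level GUD power computed here.

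**Conclusion.** The concern holds in a limited form: adequacy despite cross-over is unsupported for GUD. Under every two-sided reading examined, power at 10% cross-over is below 80%. At 7.5%, only one variant of the controls-only form passes 80%, and by less than one point. With equal cross-over in each arm, the shortfall from the stated 85% is 13 to 18 points. The first formula in section 8.2 models that case, and it is in line with sections 6.1a and 8.8.1, which count cross-over in both arms.

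It would be tempting to say that the adequacy statement is simply false and that GUD power is 72% or 67%. The documents do not support that without its condition, because the rate per arm is never fixed and the worked examples dilute controls only. The chance of missing the expected effect is therefore about 19–22% with controls-only cross-over and 28–33% with equal cross-over in each arm, against the 15% implied.

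These figures assume that the 85% is correct and undiluted, a two-sided alpha of 0.05, and an intention-to-treat comparison for GUD. They hardly depend on the unstated GUD rate or the number of men.

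**What to change.** In section 8.3:

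- Limit the statement about cross-over to balanitis.
- State the GUD rate and the cross-over assumption, including which arms it applies to.
- Report GUD power as 85% without cross-over, about 78–81% with 7.5–10% cross-over in controls only, and about 67–72% with 7.5–10% in each arm. Recompute these if the stated GUD rate does not reproduce the 85%.
- Qualify the closing sentence on adequate power to match.

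In section 8.2, remove the equality between the two dilution formulas, choose one that matches the definition of cross-over in sections 6.1a and 8.8.1, and use it throughout, including the worked values in 8.2 and 8.4.

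The cost is a less favourable stated power for GUD. No extra participants, visits or procedures are needed.
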